## 6.2 Pretreatment Preparation

### 6.2.1 Hydration

IV hydration will be given immediately prior to carfilzomib during Cycle 1. This will consist of 250 mL normal saline or other appropriate IV fluid. If lactate dehydrogenase (LDH) or uric acid is elevated (and/or in subjects considered still at risk for TLS) additional IV hydration can be considered, but with caution to avoid over hydration.

### 6.2.2 Concomitant Medications

Concomitant medication is defined as any prescription or over-the-counter preparation, including vitamins and supplements.

The following are **required** concomitant medications to be started on Cycle 1 Day 1 or up to 24 hours prior to Cycle 1 Day 1:

- Valacyclovir 500 mg PO QD or equivalent HZV prophylaxis, continuing for the duration of treatment. Additional prophylaxis is at the treating investigator's discretion.
- Patients receiving multi-agent chemotherapy are inherently at greater risk of thrombosis and should follow the anticoagulation recommendations from International Myeloma Working Group guidelines. This includes LMWH 40 mg subcutaneously daily or warfarin target INR 2-3. As an alternative to LMWH or warfarin, we would accept prophylactic doses of direct oral anticoagulants (apixaban 2.5 mg twice daily or rivaroxaban 10 mg daily). If patient is unable to receive any of the previously listed options and has no risk of thrombosis/no prior thrombosis the patient may proceed with aspirin, preferably 325 mg, after discussing with the Lead Study PI. **Patients with platelets < 30,000/mm^3 or risk of platelets dropping to Grade 3 thrombocytopenia or with active bleeding should have all anticoagulation treatment held.**

The following are **recommended** medications to be started on Cycle 1 Day 1 or up to 24 hours prior to Cycle 1 Day 1:

- Lansoprazole (Prevacid®) 15 mg PO QD, or other PO proton-pump inhibitor or H1 blocker to prevent peptic disease for the duration of treatment. Note that this is a recommended (optional) treatment.
- Mycostatin or nystatin to prevent oral thrush. Note that this is a recommended (optional) treatment.
- Allopurinol (or other approved uric acid-lowering agent) in subjects at high risk for tumor lysis syndrome due to high tumor burden may be prescribed at the treating investigator's discretion. Allopurinol should be prescribed according to the package insert.
- 

#### **Recommended Concomitant Therapy for Daratumumab SC Dosing:**

All participants will receive the following medications 1 to 3 hours prior to each study drug administration:

- An antipyretic: Acetaminophen 650 mg PO
- An antihistamine: diphenhydramine 25-50 mg IV or PO or equivalent. Avoid IV use of promethazine. After Cycle 6, if a participant has not developed an infusion-related reaction and is intolerant to antihistamines, modifications are acceptable as per investigator discretion.

- Corticosteroids as indicated in 6.3.3.
- Montelukast 10 mg PO
- For patients considered high-risk for an infusion reaction because of underlying pulmonary conditions, inhaled or nebulized albuterol along with inhaled combined long-acting beta agonist + corticosteroid can be considered at the discretion of the investigator.

### **6.2.2.1 Contraception**

Females of childbearing potential must:

- Avoid pregnancy for at least 4 weeks before beginning lenalidomide.
- Have 2 negative pregnancy tests prior to starting treatment, the first test within 10 to 14 days and the second test 24 hours before prescribing lenalidomide.
- Take pregnancy tests weekly for the first 28 days of treatment.
- Take pregnancy test every 28 days during treatment after the first month. For women of childbearing potential with irregular menstruation, pregnancy tests must be taken weekly for the first 28 days of treatment and every 14 days during treatment.
- Agree to abstain from heterosexual sexual intercourse or to use 2 methods of effective contraception beginning 4 weeks prior to initiating treatment with lenalidomide, during therapy, during dose interruptions and for 90 days following the last dose of drug (more frequent pregnancy tests may be conducted if required per local regulations). Carfilzomib is prohibited in breast-feeding women.
- Abstain from donating eggs during the study and for 90 days after last dose of study drug.

A FCBP is defined as a sexually mature female who: 1) has not undergone a hysterectomy or bilateral oophorectomy, or 2) has not been naturally postmenopausal for at least 24 consecutive months (i.e., no menses at any time in the preceding 24 consecutive months). Amenorrhea following cancer therapy does not rule out childbearing potential.

Male subjects and their partners must use 1 highly effective method of birth control plus 1 additional effective method of birth control (contraception) at the **SAME TIME** during treatment and for 90 days following the last dose of drug, even if they have undergone a successful vasectomy. Male subjects must not donate sperm during the study and for 90 days after your last dose of study drug.

Highly effective methods of contraception include:

- Intrauterine device (IUD)
- Hormonal therapy (birth control pills, injections, implants)
- Tubal ligation
- Vasectomy

Additional effective methods include:

- Latex condom
- Diaphragm
- Cervical Cap

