  13. FCBP must agree to use 2 reliable forms of contraception simultaneously or to practice complete abstinence from heterosexual intercourse during the following time periods related to this study: 1) for at least 28 days before starting lenalidomide; 2) while participating in the study; and 3) for at least 90 days after discontinuation from the study.
  14. Male subjects must agree to use 1 highly-effective method of contraception and 1 effective method of contraception at the **same time** during sexual contact with females of childbearing potential while participating in the study and for at least 90 days following discontinuation from the study even if he has undergone a successful vasectomy.
  15. All study participants in the US must be consented to and registered into the mandatory Revlimid REMS® program and be willing and able to comply with the requirements of Revlimid REMS®.
  16. Voluntary written informed consent

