## **APPENDIX 7: Lenalidomide Pregnancy Risk Minimization Plan for Celgene Clinical Trials**

### **Lenalidomide Pregnancy Prevention Plan for Subjects in Clinical Trials**

The Pregnancy Prevention Plan (PPP) applies to all subjects receiving lenalidomide within a clinical trial. The following PPP documents are included:

1. The Lenalidomide Risks of Fetal Exposure, Pregnancy Testing Guidelines and Acceptable Birth Control Methods document (Section 0) provides the following information:

- Potential risks to the fetus associated with lenalidomide exposure
- Definition of female of childbearing potential (FCBP)/female not of childbearing potential (FNCBP)
- Requirements for counseling of all subjects receiving lenalidomide about pregnancy precautions and the potential risks of fetal exposure to lenalidomide
- Acceptable birth control methods for both female subjects of childbearing potential and male subjects receiving lenalidomide in the study
- Pregnancy testing requirements for subjects receiving lenalidomide who are FCBP

2. The Lenalidomide Education and Counseling Guidance Document for each gender (female and male; Section 2 and Section 3 respectively) must be completed and signed by a trained counselor at the participating clinical center prior to each dispensing of lenalidomide. A copy of this document must be maintained in the subject's records for each dispense.

3. The Lenalidomide Information Sheet (Section 4) will be given to each subject receiving lenalidomide. The subject must read this document prior to starting lenalidomide and each time the subject receives a new supply of lenalidomide.

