### **1.2.3. Males**

Traces of lenalidomide have been found in semen. Male subjects taking lenalidomide must meet the following conditions (i.e., all males must be counseled concerning the following risks and requirements prior to the start of lenalidomide):

- Understand the potential teratogenic risk if engaged in sexual activity with a pregnant female or a FCBP
- Understand the need for the use of a condom even if he has had a vasectomy, if engaged in sexual activity with a pregnant female or a FCBP
- Understand the potential teratogenic risk if the subject donates semen or sperm.

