### **1.3.2. Male Subjects**

Male subjects must practice complete abstinence (True abstinence is acceptable when this is in line with the preferred and usual lifestyle of the subject. Periodic abstinence [e.g. calendar, ovulation, symptothermal or post-ovulation methods] and withdrawal are not acceptable methods of contraception.) or agree to use a condom during sexual contact with a pregnant female or a FCBP while taking lenalidomide, during dose interruptions and for at least 28 days after the last dose of lenalidomide, even if he has undergone a successful vasectomy.

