#### **1.5.1.2. Male Subjects**

Male subjects must agree to practice complete abstinence (True abstinence is acceptable when this is in line with the preferred and usual lifestyle of the subject. Periodic abstinence [e.g. calendar, ovulation, symptothermal or post-ovulation methods] and withdrawal are not acceptable methods of contraception.) or agree to use a condom during sexual contact with a pregnant female or a FCBP while taking

lenalidomide, during dose interruptions and for at least 28 days after the last dose of lenalidomide, even if he has undergone a successful vasectomy.

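### Read on its own, Section 6.2.2.1 accepts contraception for male subjects without a condom and is silent on a pregnant partner, whereas Appendix 7 requires abstinence or a condom

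*Protocol*

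**What the plan says.** Three places in the protocol set the rule for male subjects.

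- **Section 6.2.2.1 (Contraception):** "Male subjects and their partners must use 1 highly effective method of birth control plus 1 additional effective method of birth control". The two methods must be used at the same time, during treatment and for 90 days afterwards, and a vasectomy does not lift the requirement. The section then lists four highly effective methods (IUD, hormonal, tubal ligation, vasectomy) and three additional ones (latex condom, diaphragm, cervical cap).
- **Section 5.1, inclusion criterion 14:** "Male subjects must agree to use 1 highly-effective method of contraception and 1 effective method of contraception". This covers contact with females of childbearing potential (FCBP), also with a 90-day period. It gives no list of methods.
- **Appendix 7 (Lenalidomide Pregnancy Prevention Plan):** this plan "applies to all subjects receiving lenalidomide within a clinical trial". Section 1.2.3 says "Traces of lenalidomide have been found in semen" and requires men to "Understand the need for the use of a condom even if he has had a vasectomy". Section 1.3.2 requires complete abstinence, or that the man "agree to use a condom during sexual contact with a pregnant female or a FCBP while taking lenalidomide". Sections 1.5.1.2 and 1.5.2.2 repeat the rule. It lasts through dose interruptions and "for at least 28 days after the last dose of lenalidomide, even if he has undergone a successful vasectomy".

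For women, the bullet in 6.2.2.1 asks them to abstain or "use 2 methods of effective contraception beginning 4 weeks prior to initiating treatment with lenalidomide". Appendix 7, 1.3.1 is more specific: one of the two methods must be highly effective and the other a barrier method.

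**The concern.** The two texts have different aims. Section 6.2.2.1 is written as birth control: it seeks to prevent conception. Appendix 7 also guards against exposure of a partner, and of an existing pregnancy, through semen. An IUD, a tubal ligation, a diaphragm or a cap can serve the first aim, but none of them is the condom that Appendix 7 asks for.

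The gap is plainest when the partner is already pregnant. Birth control then has no purpose, and neither 6.2.2.1 nor inclusion 14 mentions her. Both 6.2.2.1 and Appendix 7 say their rule holds despite a vasectomy, so a reader of 6.2.2.1 alone could believe that the point behind Appendix 7 had been covered. Neither male passage refers to Appendix 7. A site working from 6.2.2.1 alone could accept a condom-free pair. What is at stake is participant and partner safety, not any estimate or test.

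**Working it through.** The protocol gives no figure to reproduce, so the check is a comparison of texts, with one count.

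**Step 1. What 6.2.2.1 accepts.** The section lists 4 highly effective and 3 additional methods.

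- All listed pairs: 4 x 3 = 12.
- Pairs with the latex condom as the additional method: 4 x 1 = 4.
- Pairs with a diaphragm or cervical cap instead: 4 x 2 = 8.

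So 8 of the 12 listed pairs contain no condom. Partner IUD plus cervical cap is a clean example, because it does not depend on how the vasectomy clause is read.

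**Step 2. The rules side by side.**

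| Feature | 6.2.2.1 | Inclusion 14 | Appendix 7, males |
|---|---|---|---|
| Condom required | No, one of three options | Not named | Yes, unless abstinent |
| Pregnant partner addressed | No | No | Yes |
| Abstinence option | Not stated | Not stated | Yes |
| Number of methods | Two | Two | Condom alone |
| Dose interruptions named | Not in the male paragraph | No | Yes |
| Period afterwards | 90 days | 90 days | At least 28 days |

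**Step 3. Which text is stricter.** The main text is looser on the type of method and on whose exposure it covers. It is stricter on the number of methods, and on duration (90 days against 28). A correction therefore has to add the condom and the pregnant partner without giving up the second method or the 90 days.

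**Step 4. Can both be met?** Yes. A man who chooses the condom as his additional method and adds a highly effective method satisfies 6.2.2.1, inclusion 14 and Appendix 7 with an FCBP partner. The 8 condom-free pairs satisfy 6.2.2.1 but fall short of Appendix 7 unless he abstains.

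**Step 5. Which of the two male passages matters more.** Section 6.3.5 says, in describing the switch to subcutaneous daratumumab, that no patients will newly start. If that means enrolment is over, the on-treatment text in 6.2.2.1 carries the practical weight, and inclusion 14 should be aligned mainly for consistency.

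**The case against.** The strongest reply is that nothing here conflicts. Appendix 7 is part of the same protocol and covers every subject on lenalidomide, so the rules add up: two methods for 90 days, one of them a condom unless the man abstains. The latex condom is the first additional method listed in 6.2.2.1. Footnote 14 of the Schedule of Events already names Appendix 7 as the place for acceptable birth control methods. Under Appendix 7 a counselling document is signed before each dispensing, an information sheet is read with each new supply, condom use after vasectomy is a counselling point, and counselling recurs at least every 28 days. Inclusion 15 makes Revlimid REMS registration mandatory for US participants.

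Most of this stands. A reader might infer that the protocol contradicts itself, but the documents do not support that, because one choice satisfies all three texts. A reader might also infer that inclusion 14 itself permits a diaphragm or cap. It lists no methods, so that reading has to be imported from 6.2.2.1. The pair of vasectomy plus diaphragm is arguable too, since the sentence in 6.2.2.1 can be read as asking for two methods on top of a vasectomy.

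What does not fall away is that 6.2.2.1, the section a site would consult on contraception, is too loose by the protocol's own standard. Footnote 14 concerns pregnancy testing in women, so it is not where staff would look for the male rule. Section 8.3.4 stops study drugs when a partner's pregnancy is reported, but it acts only after the event and does not address semen exposure of a partner who is already pregnant.

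**Conclusion.** The point holds as a modest safety inconsistency that should be corrected. Section 6.2.2.1 read alone accepts condom-free pairs and omits the pregnant partner. Inclusion 14 shares both omissions, though without a method list. Appendix 7 sets the tighter rule on type of method and gives its reason.

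Its size cannot be put in patients: the protocol does not say how many of the 45 subjects are men with a pregnant or fertile partner. The count of 8 in 12 describes the listed wording, not behaviour, and treats the lists as the menu a site would use. A reader might infer that fetal exposure is likely under this protocol. The documents do not support that, given the counselling, the REMS programme and the binding appendix. No endpoint, sample size, error rate or analysis is affected.

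**What to change.** In the male paragraph of 6.2.2.1, and in the same words in inclusion 14, state:

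*Unless completely abstinent, a male subject must use a condom at any sexual contact with a woman who is pregnant or is a FCBP, including after a successful vasectomy, throughout treatment and dose interruptions and until 90 days after the last dose. With a FCBP who is not pregnant, one highly effective method must be used at the same time in addition to the condom (see Appendix 7).*

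This keeps the two-method and 90-day requirements, supplies the abstinence option and adds dose interruptions. It is better not to add a general statement that Appendix 7 governs the type of method: for men the appendix asks only for abstinence or a condom, so such a line could be read as making a condom alone sufficient.

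Optionally, the female bullet in 6.2.2.1 could say that the two methods are one highly effective plus one barrier method, as Appendix 7, 1.3.1 already does.

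The cost is a few sentences in an amendment. Visits, sample size, analysis and timelines do not change.

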### **6.2.3 Prohibited Concomitant Medications**

Concurrent therapy with a marketed or investigational anti-cancer therapeutic is not allowed.

Corticosteroids for non-malignant conditions (e.g., asthma, inflammatory bowel disease) equivalent to a dexamethasone dose  $\geq 4$  mg/day or prednisone  $> 20$  mg/day are not permitted. Other investigational agents are not to be used during the study.

### **6.2.4 Use of Blood Products**

Subjects may receive red blood cell or platelet transfusions, if clinically indicated, per institutional guidelines. Patients who require repeated transfusion support should be discussed with the Lead Principal Investigator.

Appropriate anti-coagulation is allowed during the study (e.g.: LMW heparin, direct factor Xa inhibitors, etc.). Warfarin is allowed during the study provided that patients are monitored for INR twice a week during the first two cycles of therapy, then weekly to bi-weekly thereafter.

Patients may receive supportive care with bisphosphonates, erythropoietin, darbepoetin, G-CSF or GM-CSF, pegylated growth factors, and platelet stimulatory factors, in accordance with clinical practice or institutional guidelines prior to entry and throughout the study.

### **6.2.5 Radiation Treatment**

If clinically indicated, palliative radiation therapy to non-target lesions is permitted but study drugs should be held for 3-5 days before the start of palliative radiation therapy and 3-5 days after palliative radiation therapy.

### **6.2.6 Management of Hepatitis B Virus Reactivation**

Primary antiviral prophylaxis is permitted as per local standard of care. Per protocol, HBV DNA testing by PCR is mandatory for subjects at risk for HBV reactivation (see [Appendix 8](#)).

For subjects who are diagnosed with HBV reactivation while on treatment, study treatment should be interrupted until the infection is adequately controlled. If the benefits outweigh the risks, study treatment

may be resumed with concomitant antiviral prophylaxis as per local standard of care. Consult a liver disease specialist as clinically indicated.

### **6.3 Study Drug Administration**

#### **6.3.1 Carfilzomib Administration**

Carfilzomib for injection is supplied as a lyophilized parenteral product in single-use vials. The lyophilized product is reconstituted with water for injection to a final carfilzomib concentration of 2.0 mg/mL prior to administration. The dose will be calculated using the subject's actual BSA at baseline. Subjects with a BSA  $> 2.2 \text{ m}^2$  will receive a dose based upon a  $2.2 \text{ m}^2$  BSA. Dose adjustments do not need to be made for weight gains/losses of  $\leq 10\%$ . Subjects with a Body Surface Area (BSA) of greater than  $2.2 \text{ m}^2$  will receive a capped dose of 44 mg of carfilzomib (at the  $20 \text{ mg/m}^2$  dose level), 59.4 mg of carfilzomib (at the  $27 \text{ mg/m}^2$  dose level), or 79.2 (at the  $36 \text{ mg/m}^2$  dose level).

Carfilzomib will be given as an IV infusion over 30 minutes on Days 1, 2, 8, 9, 15 and 16 of Cycles 1- 8 and Days 1, 2, 15 and 16 of Cycles 9-24, and must be administered prior to daratumumab. If the subject has a dedicated line for carfilzomib administration, the line must be flushed with a minimum of 20 mL of normal saline prior to and after drug administration. The dose will be administered at a facility capable of managing hypersensitivity reactions. Subjects will be pre-hydrated with 250mL normal saline or other appropriate IV fluid formulation on cycle 1 Day 1. Other hydration procedures will be optional and per the discretion of the treating investigator. Subjects will remain at the clinic under observation for at least 1 hour following each dose of carfilzomib in Cycle 1 and following the dose on Cycle 2, Day 1. Subjects should be monitored periodically during this period for evidence of fluid overload. Serum chemistry values, including creatinine, must be obtained and reviewed prior to each dose of carfilzomib during Cycles 1 and 2. Refer to [Table 6-8](#) for guidance regarding dose reduction in subjects with compromised renal function.

Doses of carfilzomib may be rescheduled up to 2 days if the scheduled day falls upon a holiday or with approval from the Lead Principal Investigator. If Day 2 of Carfilzomib dosing is delayed (i.e., Day 2, 9, 16) 4 mg of dexamethasone premedication is required to be used prior to second treatment. Missed doses will not be replaced during a cycle. Carfilzomib will be escalated from  $20 \text{ mg/m}^2$  (Cycle 1 Days 1 and 2)

to 36mg/m^2 (Cycle 1 Days 8, 9, 15, 16 - see below) as long as the subject does not present with cytokine release symptoms (fever, rash, dyspnea, etc.) after Cycle 1 Day 2. If the subject does have concerning symptoms, they will be treated at 27mg/m^2 on Days 8 and 9 before being escalated to 36mg/m^2.

- Cycle 1: 20 mg/m^2 Days 1, 2; 36 mg/m^2 Days 8, 9, 15, 16. Alternatively, intermediate dose escalation (to 27mg/m^2 on Days 8, 9 of Cycle 1) will be allowed at the treating investigator's discretion.
- Cycle 2-8: 36 mg/m^2 (or best tolerated dose) Days 1, 2, 8, 9, 15 and 16
- Cycles 9-24: 36 mg/m^2 (or best tolerated dose) Days 1, 2, 15 and 16

### **6.3.2 Lenalidomide Administration**

US: Lenalidomide will be prescribed and obtained commercially in accordance with the Revlimid REMS® program of Celgene Corporation. Per standard Revlimid REMS® requirements, all investigators who prescribe lenalidomide for research subjects enrolled into this trial must be registered and must comply with all requirements of the Revlimid REMS® program. Prescriptions must be filled within 7 days. Only enough lenalidomide for one cycle of therapy will be supplied to the patient each cycle. Unused lenalidomide will be counted and documented by each site. Unused lenalidomide will be returned to Celgene by the site using instructions provided by Celgene.

Subjects will receive lenalidomide as follows in 28-day cycles:

- Cycles 1-24: 25 mg (or best tolerated dose) PO Days 1-21

Lenalidomide should be taken each evening at approximately the same time. Lenalidomide is taken with water on a full or empty stomach. Subjects should not break, chew or open capsules. If possible, late doses of lenalidomide should be taken on the assigned day but should not be made up the next day. Vomited doses will not be made up. Subjects should be instructed to never take lenalidomide past Day 21 of each cycle.

